## 2.0 STUDY OBJECTIVES

### Primary Aims:

1. Compare the task-shifting (nurse) vs. standard (physician) models on the following quality of care indicators:  
(a) depression treatment uptake, and (b) reduced depression (treatment response). *Hypothesis: Task-shifting model is associated with greater treatment uptake and depression reduction compared to standard model.*
2. Examine the relationship between change in depression and key economic and public health outcomes. *Hypothesis: Reduced depression is associated with better ART adherence, working, and more condom use.*

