**INTERVENTION:** The trial is comparing two active task-shifting implementation models of depression care: a *protocolized model* in which care is provided largely by trained nurses who act as depression care managers, and a model that relies on the *clinical acumen* of trained primary care providers (most, but not all, of whom are nurses as well). An alternative approach to the use of a structured protocol to guide depression care by non-mental health professionals, the clinical acumen model (like the protocolized model) takes an active approach to depression care by integrating a brief routine depression screening process for all patients at each clinic visit, but what the primary care provider does with this screening information is up to their discretion as opposed to following a structured protocol.

**PRIMARY OBJECTIVES:** The objectives of INDEPTH-Uganda are to compare the two task-shifting models on (1) reach (screening and follow-up rates), adoption (treatment uptake), fidelity (quality of depression care implementation by the providers), and effectiveness (alleviation of depression symptoms) implementation parameters. A secondary objective is to assess the impact of depression treatment on key economic (work) and public health (ART adherence, condom use) outcomes.

**IRB approval:** The study protocol has been approved by Institutional Review Boards at RAND Corporation (protocol # 2012-0115), Mildmay Uganda, and the Uganda National Council for Science and Technology.

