**INDEPTH (INtegration of DEpression Treatment in HIV care) Uganda** is a cluster randomized trial that attempts to identify an effective, resource-efficient model for integrating depression treatment into HIV care in low resources settings such as Uganda. In the HIV clinics of 10 healthcare facilities, the trial is comparing two active task-shifting implementation models of depression care: a *protocolized model* in which care is provided largely by trained nurses who act as depression care managers, and a model that relies on the *clinical acumen* of trained primary care providers (most, but not all, of whom are nurses as well). An alternative approach to the use of a structured protocol to guide depression care by non-mental health professionals, the clinical acumen model (like the protocolized model) takes an active approach to depression care by integrating a brief routine depression screening process for all patients at each clinic visit, but what the primary care provider does with this screening information is up to their discretion as opposed to following a structured protocol. So both of these models are active task-shifting models of depression care, as the clinical acumen model goes beyond current usual care, which relies solely on primary care provider to assess and treat, or refer to external specialists—which has resulted in depression being severely under-diagnosed and treated.

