## 3.0 STUDY DESIGN

INDEPTH-Uganda is a comparative trial that compares two active task-shifting implementation models for integrating antidepressant treatment into HIV care within 10 health care facilities in Uganda. Using a cluster randomization, 5 clinics are assigned to implement a protocolized model, and 5 others rely on the clinical acumen of trained providers. To evaluate the models, data will be collected from documentation mechanisms integrated into routine care, and from random samples of 100-150 patients enrolled at each site that screen positive for possible depression and are followed for 12 months. We will compare the two models on uptake of antidepressant treatment, and change in depression (treatment response), as well as other quality of care outcomes.

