## 9.0 STATISTICAL ANALYSES

**9.1 Power analysis for primary aims.** With 10 clusters, this study is powered to detect medium to large effect sizes; nonetheless, the results will be among the first of their kind, hence informative for subsequent analysis and policy. We calculated detectable differences for different intracluster correlation coefficient (ICC) values. Data from developing countries indicate low correlations of health outcome variables within primary care settings (improving power), including .03 for depression in a collaborative care trial in India, and .011 for maternal/perinatal health outcomes in 8 Latin American countries. ICC tends to be higher for process related measures (which would include the focus of Aim 1a): median=.16 for the same 8 country study.

**Aim 1a (treatment uptake):** With 150 patients per site and assuming 30% antidepressant uptake in the standard model and ICC=.16, we will be able to detect an increase of 28% in uptake rates between the task-shifting and standard clinics ( $\alpha = .05$ , 80% power; one sided test). For ICC=.25 the increase is 34%. Given the systematic procedural difference in the two arms, we expect the actual difference may exceed these amounts.

**Aim 1b (depression change):** For measuring change in PHQ-9 in an intention to treat (ITT) analysis using the whole sample, with ICC =.025, s.d. =3.9 (from our current study), and 10% attrition, we'll have power to detect a 1.26 difference on the PHQ-9 ( $\alpha = .05$ , 80% power; 2-sided

test); for ICC=.01 and .05, detectable differences are .92 and 1.71. For analysis of those receiving antidepressants, we estimate 30% (n=45) of the standard arm patients will be treated (a larger share is expected in the task-shifting arm, which will improve power). With ICCs =.01, .025, and .05 (s.d. = 3.0), and 10% attrition, we will be able to detect changes of 1.00, 1.20, and 1.46 in the PHQ-9. These correspond to medium effect sizes (Cohen's *d*) of 0.33, 0.40 and 0.49.

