### 11.4 Importance of the Knowledge to Be Gained

If we demonstrate that the task-shifting approach to depression treatment is feasible, effective and well incorporated into clinic systems, it will establish a model that addresses the human resource challenges to building the capacity for sustainable depression treatment. Findings will have implications not only for PLHA in SSA, but also other developing regions, non-HIV populations, and treatment of other diseases.

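### Primary Aim 1 is worded against a standard physician arm that the trial does not randomise, and the Overview and Section 2.0 rank the outcomes differently

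*Protocol*

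**What the plan says.** **The contrast.** Section 2.0 gives Primary Aim 1 as "Compare the task-shifting (nurse) vs. standard (physician) models on the following quality of care indicators", with the hypothesis "Task-shifting model is associated with greater treatment uptake and depression reduction compared to standard model". Section 3.0 describes the allocation as "5 clinics are assigned to implement a protocolized model, and 5 others rely on the clinical acumen of trained providers". The Introduction adds "So both of these models are active task-shifting models of depression care, as the clinical acumen model goes beyond current usual care".

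The wording of Section 2.0 recurs later in the protocol:

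- Section 9.1 sizes Aim 1a "assuming 30% antidepressant uptake in the standard model", and uses the same 30% to estimate how many comparator patients will be treated.
- Section 9.2 compares task-shifting with control or standard arms.
- Sections 11.2 and 11.5 describe monitoring in the comparator as usual care under a physician-driven model.
- Section 11.4 states what success would mean: "If we demonstrate that the task-shifting approach to depression treatment is feasible, effective and well incorporated into clinic systems".

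**The outcomes.** The Overview lists reach, adoption, fidelity and effectiveness as primary objectives and then says "A secondary objective is to assess the impact of depression treatment on key economic (work) and public health (ART adherence, condom use) outcomes". Section 2.0 has two Primary Aims. The first covers treatment uptake and depression reduction. The second is the economic and public health question.

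**The concern.** An aim and its hypothesis fix what a trial may conclude. Here they name a comparator, standard physician care, that the design sections do not contain, and they name task-shifting as the feature under test although both arms have it. A report that followed Section 2.0 literally would credit a positive result to task-shifting, or read a null result as task-shifting failing to improve on physician care. Neither conclusion would follow from the randomised comparison.

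The two outcome lists raise a second difficulty. A reader cannot tell from the protocol whether reach and fidelity are primary, or whether the economic and public health question is primary or secondary.

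**Working it through.** **1. What separates the arms**

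| Feature | Protocolized | Clinical acumen | Source |
|---|---|---|---|
| Called task-shifting | Yes | Yes | Overview, 1.0, 3.0 |
| Routine PHQ-2 screening of all adults | Yes | Yes | 6.1, 6.2 |
| Monthly on-site psychiatrist supervision | Yes | Yes | 6.2, 6.3 |
| Start-up training | Yes | Very similar, without the structured protocol | 6.3 |
| Who provides depression care | Nurses, with oversight by the officer in charge | All primary care providers: nurses and clinical/medical officers | 6.2 |
| Evaluation and treatment after a positive screen | By structured protocol | At the provider's discretion | 6.1, 6.2 |

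Only the last two rows differ, and the staffing row differs in part. Section 4.0 gives one clinical or medical officer with 3 to 5 nurses at the larger clinics and with 2 to 3 at the smaller ones. The nurse share of those staff is therefore 3/4 to 5/6 (75% to 83%) at larger clinics and 2/3 to 3/4 (67% to 75%) at smaller ones. This agrees with the Introduction, which says that most clinical acumen providers are nurses. Neither task-shifting versus standard nor nurse versus physician describes this contrast.

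**2. Where the older contrast carries planning content**

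- *Section 9.1:* the 30% uptake is attached to the standard model. No basis is given for it as a rate in trained, screened and supervised clinics.
- *Section 9.2:* formal evaluation is not analysed separately, partly because it would be hard to establish what the doctor did in the standard arm. The example of an arm-by-sex interaction relies on nurses being largely female. Both points assume a physician comparator.
- *Sections 11.2 and 11.5:* comparator monitoring is described as part of usual care. Section 4.0 says these clinics provided no depression care before the study, and Section 6.2 describes a supervised, trained model. These passages must be reconciled.

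**3. The two outcome lists**

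| Outcome | Overview | Section 2.0 |
|---|---|---|
| Uptake (adoption) | Primary | Primary (Aim 1a) |
| Depression reduction (effectiveness) | Primary | Primary (Aim 1b) |
| Reach | Primary | Not listed |
| Fidelity | Primary | Not listed |
| Economic and public health | Secondary | Primary (Aim 2) |

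The lists agree on the first two rows and differ on the other three.

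**4. Does the comparator label affect power?**

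Inputs from Section 9.1: 150 patients per clinic, ICC 0.16, 30% comparator uptake, one-sided 0.05, 80% power. With five clinics per arm, the effective sample size per arm is 5 × 150 / (1 + 149 × 0.16) = 750 / 24.84 = 30.2.

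The detectable difference d, with p1 = p0 + d and p̄ the mean of p0 and p1, solves

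d × √30.2 = 1.645 × √(2p̄(1 − p̄)) + 0.842 × √(p0(1 − p0) + p1(1 − p1)).

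At p0 = 0.30 this gives d = 0.313 (0.303 with an unpooled variance). The protocol states 28 points, which I could not reproduce. That discrepancy is a separate matter and is not evidence for this point.

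| Comparator uptake | 20% | 30% | 40% | 50% |
|---|---|---|---|---|
| Detectable difference (points) | 30.0 | 31.3 | 31.2 | 30.0 |

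The difference to be detected hardly moves over this range, which is my own choice.

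**The case against.** The strongest reply is that this is only terminology. The old labels map one to one onto the arms. Task-shifting is the arm with the depression care manager (Sections 8.0 and 11.2), whom the Introduction places in the protocolized model. Standard is the other arm: Section 11.2 says its primary care providers will be trained in antidepressant use and monitoring, which fits Section 6.2. The randomised comparison and the model in Section 9.2 can be estimated unchanged. All of this stands, so a reader who infers that Aim 1 cannot be answered goes too far.

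A reader might also infer that the primary result could be chosen after the data are seen, or that type I error is uncontrolled. The documents do not support that. Uptake and change in depression are the named comparison in the Overview's design paragraph and in Section 3.0, appear in both outcome lists, and are the only outcomes powered in Section 9.1. Test order and alpha allocation are commonly left to an analysis plan, which is not at hand.

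Nor do the documents show that 30% is the wrong rate. Given the absence of depression care before the study and the severe under-treatment that the Introduction describes, 30% may fit an active arm at least as well as usual care.

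The reply does not reach the conclusion to be drawn. Mapping the labels recovers the arms, but it does not make the hypothesis in Section 2.0 or the message in Section 11.4 follow from comparing two task-shifting models. It also leaves the two outcome lists in conflict.

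**Conclusion.** Wrong as written on two counts. First, the stated aim, hypothesis and planned conclusion concern task-shifting against standard physician care, while the trial can inform only protocolized against clinical acumen care. Second, the Overview and Section 2.0 contradict each other on reach, on fidelity and on the rank of the economic and public health question.

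The size is one of interpretation. The estimate is unaffected, and the detectable uptake difference varies by little more than one point over comparator rates of 20% to 50%. That last statement rests on a normal approximation at ICC 0.16 with 150 patients per clinic. The two main findings rest on the text alone. The point should be corrected, but it does not invalidate the design.

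**What to change.** - Restate Primary Aim 1, its hypothesis and the arm labels in Sections 9 and 11 as protocolized versus clinical acumen. Limit the conclusion in Section 11.4 to that contrast.
- Reconcile the descriptions of comparator monitoring in Sections 11.2 and 11.5 with Section 6.2.
- State in Section 9.1 that the 30% uptake refers to the clinical acumen arm, and tabulate the detectable difference over a range of rates, for example 20% to 50%.
- Give one outcome list for the Overview and Section 2.0. Uptake and PHQ-9 change are the natural primaries, being common to both lists and the only outcomes powered. Reach, fidelity and the present Aim 2 would then be secondary.

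The cost is a wording amendment and a small table. No patients, visits or data collection are added.

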## 3.0 STUDY DESIGN

INDEPTH-Uganda is a comparative trial that compares two active task-shifting implementation models for integrating antidepressant treatment into HIV care within 10 health care facilities in Uganda. Using a cluster randomization, 5 clinics are assigned to implement a protocolized model, and 5 others rely on the clinical acumen of trained providers. To evaluate the models, data will be collected from documentation mechanisms integrated into routine care, and from random samples of 100-150 patients enrolled at each site that screen positive for possible depression and are followed for 12 months. We will compare the two models on uptake of antidepressant treatment, and change in depression (treatment response), as well as other quality of care outcomes.

## 4.0 STUDY SETTING

The study is being conducted in collaboration with Mildmay Uganda, a non-government organization that provides holistic outpatient HIV care at its own clinics, trains healthcare workers throughout Uganda and the region, and provides technical assistance in HIV care to healthcare facilities across Uganda. Of the 10 healthcare facilities participating in the study, eight are run by the Ministry of Health and two are private, faith-based, not-for-profit healthcare facilities; two are district hospitals and the others are designated as health centre III or IV facilities by the Uganda Ministry of Health, and are located in the districts of Mpigi, Mityana, Luweero, and Wakiso. Each facility is a hospital that operates an HIV clinic on specific designated days of the week, and it is in these clinics that depression care is being integrated as part of this study. The 6 larger clinics operate 2-3 days per week and generally have 1 clinical or medical officer and 3 to 5 nurses to provide primary HIV care to a clientele ranging from 1500-3000 clients and 80-120 patients are seen each clinic day. The 4 smaller clinics operate one day per week and are manned by 1 clinical or medical officer and 2-3 nurses; client base ranges from 350-1000, with 40-60 patients seen each day.

Consistent with task-shifting approaches becoming increasingly common in the context of ART scale-up across the region, at all sites nurses serve as primary care providers (along with the clinical/medical officers), and manage the prescription and monitoring of ART and other common HIV medications; more complex conditions or complications that arise are typically managed by the clinical/medical officer. All clinics have expert clients (volunteer experienced HIV clients who display exemplary HIV care adherence and are trained to provide peer support and assist in lower level tasks) and village health team (VHT) workers (community lay volunteers) who volunteer to take on tasks such as triage assessments, filing and retrieving charts, and keeping the clinic clean. No psychiatric or depression care services were being

provided at these clinics prior to the study; clients who developed significant psychiatric symptoms are referred to the nearest district or regional hospital for care.

## **5.0 SELECTION AND ENROLLMENT OF PARTICIPANTS**

Over the course of 12 months at each site, research coordinators (Masters level graduates with social science training) will recruit random samples of 100-150 patients who the triage personnel screen as positive for potential depression (PHQ-2 > 2), who are confirmed to be positive in the research coordinator's own PHQ-2 administration, and who are determined to be medically stable.

A cohort of providers from each site will also be enrolled and followed over the 24-month implementation to examine change in knowledge, attitudes and practices regarding depression care and perceived impact of the implementation on clients, providers and clinic operations.

All patient and provider participants will provide written informed consent prior to enrollment.

### **5.1 Recruitment and enrollment process:**

The consent forms and IRB protocol for the study will be submitted for review and approval by the RAND IRB, and the IRB used by Mildmay (Makerere University, Faculty of Medicine). Once approval is obtained from these IRBs, the protocol will be sent to the Uganda National Council of Science and Technology for final approval (this typically takes no longer than one month).

#### ***HIV care providers***

We will approach clinic staff (DCM nurses, primary care providers) at the participating sites to participate in the study by providing self-report data on their experience with the depression treatment models. Written informed consent will be obtained. It will be made clear that their participation is voluntary and that there will be no ramifications related to their job, job evaluation, or otherwise if they decide not to participate in the research data component.

#### ***HIV patients***

Patients who have screened positive for depression on the routinely administered PHQ-2 will be informed of the study by one of their providers (nurse or doctor). If interested in participating in the study the patient will be referred to the site coordinator for a detailed description of the study, confirmation of eligibility and consent procedures. It will be made clear to patients that their decision of whether to participate or not will have no impact on their clinical care or ability to receive depression treatment if needed. The site coordinator will describe the details of the study, including the nature of the patient's involvement in the study, the possible risks and benefits of participation, and the patient's ability to withdraw from the study at any time without consequence. The patient will have the opportunity to ask questions about the study, after which informed consent will be obtained and documented by having the patient read and sign a consent form, which will be stored in a locked file cabinet. Each participant will be given a copy of the consent form to keep. No modifications or waivers of the elements of consent or the requirement for documentation of consent have been requested from our Institutional Review Board.

**5.2 Participant tracking procedures** Contact information (address, phone numbers) will be collected at enrollment and verified at follow-up visits. We will collect contact info of two people who are likely to know how to reach the participant if needed, and will ask participants what to say, and avoid saying, when contacting them.

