## 6.2 Clinical Acumen Model

Although psychiatric treatment is generally not currently available in HIV clinics (nor general primary care clinics) in Uganda, clinics that are looking to increase their provision of depression treatment are likely to follow the model used in many other parts of the world, which is to train primary care providers to identify and treat depression. Similarly, the clinical acumen model of depression care relies on the discretion of primary care providers who receive depression care training to provide depression diagnosis and treatment as deemed warranted. To facilitate this

process, like the protocolized model, the clinical acumen arm also includes routine screening of all adult clients and monthly on-site supervision from study psychiatrists. However, this model relies on the clinical judgment of the primary care provider to decide whether to further evaluate and treat patients who screen positive for possible depression, as opposed to a structured protocol (see Table 1 for an outline of the model and how it compares to the protocolized model). Another difference between the models is that depression care is managed entirely by nurses (with oversight from the clinical/medical officer in charge) in the protocolized model, whereas in the clinical acumen model all primary care providers (who are comprised of nurses and clinical/medical officers) are expected to provide depression care.

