## 7.0 DATA SOURCES

To evaluate the two task-shifting models, we will compare the implementation, effectiveness, and cost-effectiveness of these models over a 24-month period. Using the RE-AIM framework, we will evaluate the *reach* of depression screening and treatment, *adoption* of depression treatment knowledge and intervention by providers, *quality of implementation* (fidelity to depression care model), and *effectiveness* of depression treatment on patient outcomes. As outlined in Table 2, these implementation domains and corresponding outcomes will be assessed from data triangulated from these data sources: (1) data abstracted from data collection mechanisms integrated into routine care; (2) monthly logs summarizing chart abstracted data completed by the supervising psychiatrists; (3) survey data from a longitudinal cohort of randomly selected patients at each site who screen positive for potential depression (PHQ-9 > 2); and (4) survey data from longitudinal cohort of providers involved in provision of depression care at each site. Survey data from the patient cohort will also be used to assess how change in depression is related to key economic and public health outcomes. These data sources are described in more detail below.

**Routine data abstraction:** We will assess the implementation of screening (% of adults screened; % screened who screen positive) by abstracting data from the Triage Book, which the triage station at each site uses to list the clients who attend each day of the clinic, their vital signs, and PHQ-2 score. PHQ-9 and MINI administration data will be recorded in the patient's clinic chart. Depression Treatment Registry books will be installed at each site for providers to document clients who have started antidepressant therapy and their depression diagnosis, and records of each follow-up visit that include PHQ-9 score, presence of side effects and medication and dose prescribed.

**Supervision log data:** From the chart reviews that the supervisors conduct each month at each site, monthly aggregate scores are recorded for newly prescribed patients (number with correct diagnosis, correct prescribed antidepressant, and correct prescribed dosage) and patients in ongoing treatment (number correctly assessed for depressive symptoms and side effects; number correctly dosed; and number who returned for scheduled follow-up visit in past month).

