***Confidentiality.*** To protect confidentiality, the following steps will be taken: All research data will be kept in locked file cabinets and will be available only to research staff directly involved in this project. Data will be identifiable only by study numbers and patient initials. HIV status will not appear along with any personal identifying information. The hand-held computer devices used to administer the computer-assisted personal interviews (at baseline and Months 6 and 12) will not collect any identifying information; only the study ID number and patient initials will be entered into these devices. The data on these hand-held computers will be password-protected and data will be uploaded to a study desktop computer on a daily basis. Personal information including subject's name, address, and phone number will be entered on a tracking form, stored separately from all research data, and kept in a locked file cabinet at the study site. Research interview data collected from the participants will be kept confidential and not be shared with the patient's physician or other clinic staff; the exception is the depression and psychiatric measures (PHQ-9, MINI, side effect measure), which will be shared with the patient's providers in order to optimize depression treatment. Patients will be informed of these conditions during the informed consent process.

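### The patient cohort is called random but is recruited through treating providers who know the arm, and research PHQ-9 results return to those providers even where further evaluation is meant to be at their discretion

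*Protocol*

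**What the plan says.** **Sampling.** Protocol section 5.0 says that research coordinators "will recruit random samples of 100-150 patients who the triage personnel screen as positive for potential depression", confirmed by the coordinator's own PHQ-2 and medically stable. The Study Overview and section 3.0 also speak of random samples, and section 7.0 lists "survey data from a longitudinal cohort of randomly selected patients at each site".

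**Recruitment.** Section 5.1 (HIV patients) gives the only procedure. Patients with a positive routine PHQ-2 "will be informed of the study by one of their providers (nurse or doctor". Then: "If interested in participating in the study the patient will be referred to the site coordinator", who explains the study, confirms eligibility and takes consent.

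**Knowledge of the arm.** Clinics are randomised, and section 6.3 trains staff in separate workshops for each arm.

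**Feedback.** Section 7.0 puts a PHQ-9 in the research survey at baseline and months 6 and 12, as an independent assessment of depression. Section 11.2 keeps research interview data from clinic staff, but "the exception is the depression and psychiatric measures (PHQ-9, MINI, side effect measure), which will be shared with the" patient's providers. It makes no distinction by arm.

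**The comparator.** Section 6.2 says of the clinical acumen arm that "this model relies on the clinical judgment of the primary care provider to decide whether to further evaluate and treat patients" who screen positive. In the protocolized arm, section 6.1 sends every medically stable screen-positive patient to the nurse for evaluation.

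**The concern.** There are two separate problems, and both bear on the sample used for Aims 1a and 1b.

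First, a random sample needs a list, a draw and a record of what happened to those drawn. Section 5.1 has none of these. Entry runs through a treating provider and then through the patient's interest, after clinics have been allocated and with the provider aware of the arm. If willingness to mention the study goes with willingness to treat, and this differs between arms, the enrolled patients are not comparable. Adjusting for age, sex and physical health, the covariates that section 9.2 gives as examples, would not capture it.

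Second, the clinical acumen model is defined by leaving further evaluation to the provider. If the research interview supplies a full PHQ-9 score to that provider, cohort members receive something that other patients of the clinic do not. In the protocolized arm the same information largely duplicates care. The expected effect is higher uptake in the acumen arm and a smaller contrast.

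**Working it through.** **1. Sampling text side by side.**
- The Study Overview and sections 3.0, 5.0 and 7.0 claim random samples or random selection.
- Section 5.1 goes from positive screen, to information from a provider, to patient interest, to the coordinator. It describes no draw, sampling list or log.
- The coordinator's repeat PHQ-2 (section 5.0) checks eligibility. It does not show who was or was not told of the study.

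**2. Feedback text side by side.**
- Section 7.0 lists the PHQ-9 among the survey measures but not the MINI. Section 11.2 names both as shared. The PHQ-9 is therefore the firm part of this point, and the MINI counts only if the coordinator administers it.
- A PHQ-9 followed by MINI criteria is the evaluation step of the protocolized model (section 6.1). Section 6.2 makes that step optional in the acumen arm.

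**3. The plan's own power figure.** Section 9.1 assumes 150 patients per site, 30% uptake in the standard arm, ICC .16, one-sided alpha .05 and 80% power, and states a detectable increase of 28 points. I read its standard and task-shifting arms as the acumen and protocolized arms. Section 3.0 gives 5 clinics per arm.

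Effective n per arm = 5 × 150 / (1 + 149 × 0.16) = 750 / 24.84 = 30.2.

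Solving for 80% power gives 31.3 points (pooled variance) or 30.3 (unpooled), so the stated 28 is not reproduced. Six clinics per arm with unpooled variance would give 27.8, but the protocol has five. That is a separate matter. It matters here only because the baseline power at 28 points is 72% to 74%, not 80%.

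**4. Sensitivity to a shift in acumen uptake.** Assumption: protocolized uptake stays at 58% (30 + 28). In unpooled form:

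power = Φ( d / √{[p0(1 − p0) + p1(1 − p1)] / 30.2} − 1.645 )

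For 30% v 58%: 0.28 / √(0.4536 / 30.2) = 0.28 / 0.1226 = 2.284, and Φ(2.284 − 1.645) = 0.74.

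| Observed acumen uptake | Difference (points) | Power, pooled | Power, unpooled |
|---|---|---|---|
| 20% | 38 | 93% | 95% |
| 25% | 33 | 85% | 87% |
| 30% | 28 | 72% | 74% |
| 35% | 23 | 56% | 58% |
| 40% | 18 | 40% | 41% |
| 45% | 13 | 26% | 27% |

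From 30% upward, each 5-point rise costs 14 to 17 points of power. The two rows below 30% show selection running the other way.

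**5. Does selection have a direction?** Suppose treated patients are referred r times as often as untreated ones. Observed uptake is then p·r / (p·r + 1 − p). The ratio r is an assumption.
- r = 1.5, acumen arm: 0.45 / 1.15 = 39.1%. Protocolized arm: 0.87 / 1.29 = 67.4%.
- r = 2, acumen arm: 0.60 / 1.30 = 46.2%. Protocolized arm: 1.16 / 1.58 = 73.4%.

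With the same ratio in both arms the difference is 28.3 or 27.3 points and unpooled power is 74% or 73%, almost unchanged from 28 points and 74%. With the ratio acting in the acumen arm only, the difference would be 58 − 39.1 = 18.9 or 58 − 46.2 = 11.8 points. The effect depends on how the ratio differs between arms, and the protocol says nothing on that.

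**The case against.** Section 5.1 says that screen-positive patients will be informed. It gives providers no stated choice over whom to tell, and patient interest filters any consented sample, including one drawn at random. Providers are the first contact in both arms. In protocolized clinics, a patient who never reaches the nurse is also less likely to be both informed and treated, so selection need not favour one arm. This stands, and it removes any claim to know the direction. It does not explain the word random, and nothing checks that every positive patient is told.

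On feedback, the sharing applies in both arms and is disclosed at consent. A score is not a treatment decision, and it could also prompt treatment of protocolized patients whom the nurse missed. This also stands in part: the decision remains with the provider, and protocolized uptake might move as well. But protocolized patients are already due a full evaluation, so the added information should matter more in the acumen arm.

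A reader might infer that providers choose who hears of the study, that both routes inflate acumen uptake, and that power falls to 41% or 27%. The documents do not support this. No discretion is stated, the selection route has no established direction, and those power figures need acumen uptake of 40% or 45% with protocolized uptake fixed at 58%, neither of which the protocol establishes.

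**Conclusion.** The point holds in two parts of different strength.

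The claim of random sampling is contradicted by the only recruitment procedure described. The cohort is open to recruitment bias after randomisation by people who know the arm. Its direction and size are unknown.

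The sharing of research PHQ-9 results conflicts with the discretion that defines the clinical acumen arm. It probably raises acumen uptake and biases the contrast towards no difference. The direction is a reasoned expectation, and the protocol gives no amount. The loss of about 15 points of power per 5-point rise is an illustration that rests on ICC .16, 150 patients per site, five clinics per arm and protocolized uptake fixed at 58%.

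I take the cohort to be the Aim 1a sample because section 9.1 sizes that aim on 150 patients per site. The effect on Aim 1b is argued in kind only.

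**What to change.** 1. **Sampling.** Amend section 5.1 to match 5.0. The coordinator draws patients at random from the day's Triage Book entries with PHQ-2 of 3 or more. The coordinator or triage staff make the first approach, and eligibility is then confirmed as now. Numbers drawn, approached, declined and enrolled are logged by clinic and arm.
2. **Feedback.** Reconcile section 11.2 with 6.2, and make clear whether the coordinator administers the MINI. If sharing stays, state that cohort uptake in the acumen arm estimates clinical acumen plus a research-supplied assessment. What providers should see is for the investigators and IRBs to settle.
3. **Supporting analysis.** Report uptake from the Triage Book and the Depression Treatment Registry, which section 7.0 already installs "for providers to document clients who have started antidepressant therapy and their depression diagnosis". This should support the cohort analysis and not replace it. It would use records of patients who did not consent, section 5.1 says no waiver was requested, and the IRBs would have to agree. Triage positives also include medically unstable patients, and the Triage Book fields listed in 7.0 do not include age or sex.

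**Cost.** A little coordinator work and no extra staff, record linkage for item 3, possible changes to consent and IRB wording, and a narrower cohort uptake claim if sharing stays.
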